## Abstract

**Background:**

Age-related alterations in metabolism and excretion of medications increase the risk of adverse drug events in the elderly. Inappropriate polypharmacy and prescription practice entails increased burdens of impaired quality of life and drug related morbidity and mortality. The main objective of this trial is to evaluate effects of a tailored educational intervention towards general practitioners (GPs) aimed at supporting the implementation of a safer drug prescribing practice for elderly patients ≥ 70 years.

**Methods/design:**

Approximately 80 peer continuing medical education (CME) groups (about 600 GPs) in southern Norway will be recruited to a cluster randomized trial. Participating groups will be randomized either to an intervention- or a control group. The control group will not receive any intervention towards prescription patterns in elderly, but will be the target of an educational intervention for prescription of antibiotics for respiratory tract infections. A multifaceted intervention has been tailored, where key components are educational outreach visits to the CME-groups, work-shops, audit and feedback. Prescription Peer Academic Detailers (Rx-PADs), who are trained GPs, will conduct the educational outreach visits. During these visits, a set of quality indicators (QIs), i.e. explicit recommendations for safer prescribing for elderly patients, will be presented and discussed. Software will be handed out for installation in participants' practice computers to enable extraction of pre-defined prescription data. These data will subsequently be linked to corresponding data from the Norwegian Prescription Database (NorPD). Individual feedback reports will be sent all participating GPs during and one year after the intervention. Feedback reports will include QI-scores on individual- and group levels, before and after the intervention. The main outcome of this trial is the change in proportions of inappropriate prescriptions (QIs) for elderly patients ≥ 70 years following intervention, compared to baseline levels.

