## Methods

### Design

Our hypothesis is that an educational intervention program carried out during a 6-month period will be effective in improving prescribing patterns by reducing the occurrence of potentially targeted harmful drugs and drug-drug interactions in elderly patients.

Our main hypothesis will be tested using a cluster-randomized controlled trial comparing outcomes between the intervention and control groups at follow-up. Peer continuing medial education (CME) groups of GPs will be randomized to receive a tailored intervention to support a safer prescription practice for the elderly or to a control group. The control group will be assigned to another trial, namely an educational intervention for better prescription of antibiotics for respiratory tract infections [44]. As such, the control group may also be susceptible to changes in their general prescription patterns, i.e. a possible Hawthorne effect. To control for this, we will be able to analyze prescription patterns for *all *Norwegian GPs not included in the current trial, using data from the Norwegian Prescription Database (NorPD), a national registry including data for all prescription drugs issued at Norwegian pharmacies, established in 2004 [45].

Prescription data will be collected for all eligible patients from intervention- and control group GPs at baseline and one year after the initiation of the trial. Changes in prescribing patterns will be tracked by a set of explicit recommendations (quality indicators) developed by the authors (Table 1), which will be used to analyze changes in baseline and post-intervention prescribing patterns. Degree of improvements will be measured by recording prescriptions of the particular drugs and the concurrent use of listed drug combinations that the GPs have been recommended to avoid.

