### Outcome measures

Primary outcome measures will be changes in prescription patterns after the tailored educational intervention regarding the listed QIs (Table 1). Post-intervention prescription data will be collected one year after the collection of the baseline prescription data. Prescription patterns in the intervention group will be compared with the non-intervention control group, and with corresponding data (from NorPD) based on a random sample of Norwegian GPs not included in the current trial.

In addition to investigating changes in each QI, we will summarize changes for all QIs (Table 1), in order to give a total sum score for improvement potentials. The difference in total QI sum score between the intervention group and the control group will be a main outcome measure. The QI regarding regular use of the EPR function showing patient's total regular medications will not be included in this sum score. Outcome measures are summarized in Table 2.

It would also be interesting to investigate if this intervention may influence all-over mortality patterns for elderly patients targeted during this intervention as compared to corresponding elderly patients in the control group [44]. By 2006, death data are not yet included in the NorPD, but efforts are currently undertaken to include such data in the NorPD on a regular basis. A possible mortality study has not yet been elaborated in details, but this will be considered.

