### Sample size and statistics

In a pilot study (including 13 physicians) for the present study, the mean number of positive hits on our listed QIs (Table 1) made up 25 hits per 100 elderly patients during the preceding 12 months period. In accordance with this finding, we anticipate an occurrence of inappropriate prescription of about 25 hits per 100 elderly patients in the present study.

Proving a clinical relevant reduction from 25 to 17 hits or less per 100 patients (32% relative reduction), assuming that the prevalence of inappropriate prescriptions in the control group remains constant, will imply a need for 74 peer groups in total (power of 80%; statistical significance level of 5%). This estimation takes into account the need to adjust for intra-cluster correlation, since data within the peer CME groups cannot be assumed to be independent. Furthermore, we assume the average number of GPs per peer CME group to be 7 (allowing for some withdrawals) and that the average number of patients ≥ 70 years per participating GP during the study period will be 165. Based on previous studies [46,58], the intracluster correlation coefficient is assumed to be 0.085, resulting in a variance inflation factor of 99 [59].

We will carry out post-test comparisons between the intervention and control group using cluster-adjusted chi-square and *t*-tests. Analysis of covariance may be used to adjust for imbalance of baseline levels between the intervention- and control-groups [60]. The data set will primarily be analyzed according to the cluster randomization, however, analyzes at physician- and sub-groups of physicians as well as compared to NorPD-data for GPs not participating in the study, will also be performed.

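### The main outcome is stated inconsistently, and the stated power covers only one version: QI hits per 100 patients compared between arms at follow-up

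*Protocol article*

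**What the plan says.** The Protocol article describes its main outcome in four places.

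- **Abstract, Methods/design.** The main outcome is "the change in proportions of inappropriate prescriptions (QIs) for elderly patients" after the intervention, set against baseline levels. The sentence mentions neither a control group nor a denominator.
- **Design.** The main hypothesis is tested by "comparing outcomes between the intervention and control groups at follow-up". The same section warns that control GPs, who receive a different educational programme, may also change their prescribing.
- **Outcome measures.** "Primary outcome measures will be changes in prescription patterns after the tailored educational intervention regarding the listed QIs", with a comparison against the control group. The section then adds: "The difference in total QI sum score between the intervention group and the control group will be a main outcome measure". One QI, on use of a record-system function, is left out of the sum. The text gives the sum score no unit.
- **Sample size and statistics.** "we anticipate an occurrence of inappropriate prescription of about 25 hits per 100 elderly patients in the present study". The target is a fall from 25 to 17 hits per 100 patients, a relative reduction of 32%, and the calculation takes the control arm as stable, "assuming that the prevalence of inappropriate prescriptions in the control group remains constant". The trial size that results is "74 peer groups in total (power of 80%; statistical significance level of 5" per cent. The planned tests compare the arms after the intervention. Analysis of covariance is mentioned only as something that may be used if baseline levels are imbalanced.

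**The concern.** These statements differ in two respects that matter for the primary result.

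The first is the contrast. A change from baseline within the intervention arm, a difference between arms in change, and a difference between arms at follow-up are three different estimators. The first is not protected by randomisation. The other two estimate the same effect but have different precision.

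The second is the quantity. The text offers a proportion without a denominator, changes in each of 14 indicators, a sum score without a unit, and hits per 100 patients. Nothing says which one the trial's conclusion rests on.

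At stake are the meaning of the 80% power and the freedom to choose. If the main outcome is not the quantity that was powered, the power statement does not describe it. If several versions remain open, the main result can be selected after the data are seen. Leaving baseline adjustment to observed imbalance adds a further data-dependent choice.

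**Working it through.** **Inputs, all from Sample size and statistics:** 25 versus 17 hits per 100 patients; significance level 5% (sidedness not stated; two-sided used here); power 80%; 7 GPs per group; 165 patients aged 70 or over per GP; intracluster correlation 0.085; variance inflation factor 99.

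**Step 1: reproduce the 74 groups.**
- Cluster size: 7 × 165 = 1,155 patients.
- Variance inflation: 1 + (1,155 − 1) × 0.085 = 99.09 (stated: 99).
- Patients per arm for 0.25 versus 0.17, ignoring clustering, with continuity correction: 431.
- Groups per arm: 431 × 99 / 1,155 = 36.94, so 37, or 74 in total. This matches.

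Without the continuity correction, 406 patients per arm gives 406 × 99 / 1,155 = 34.8, so 70 groups. One-sided versions give about 55 groups, or 59 with the correction. None of these matches 74. The plan's figure is therefore a two-sided comparison of two arms at one time point, with hits per patient treated as a proportion. No baseline measurement and no correlation between baseline and follow-up enters it. No sample size can be derived for a share of prescriptions, because the number of prescriptions per patient is not given.

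**Step 2: change from baseline against between-arm difference when controls drift.** Suppose the intervention arm goes from 25 to 17. Its change from baseline is 25 − 17 = 8 per 100 whatever the controls do. The between-arm difference is the control rate at follow-up minus 17. The control falls below are assumptions.

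| Assumed fall in controls | Control rate at follow-up | Change in intervention arm | Between-arm difference |
|---|---|---|---|
| 0% | 25.00 | 8 | 8.00 |
| 5% | 23.75 | 8 | 6.75 |
| 10% | 22.50 | 8 | 5.50 |
| 20% | 20.00 | 8 | 3.00 |

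The two agree only in the first row, which is the constant-control assumption of the sample-size section.

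**Step 3: precision of the between-arm options.** Let ρ be the correlation between a group's baseline and follow-up rates (not given in the protocol). Relative to a follow-up-only comparison, the variance of a between-arm difference in change is 2(1 − ρ). With the baseline rate as covariate it is 1 − ρ², apart from a small loss of degrees of freedom. Since 1 − ρ² ≤ 1, and 2(1 − ρ) − (1 − ρ²) = (1 − ρ)² ≥ 0, the covariate analysis is never the less precise of the three in this approximation. The change score is worse than the follow-up comparison whenever ρ is below 0.5.

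**Side note on the 74.** Hits are counts, and one patient can have more than one. A Poisson calculation with the same inflation gives 515 patients per arm before clustering, and 2 × 515.08 × 99.09 / 1,155 = 88.4, so 90 groups when rounded up in each arm. This is a separate matter and does not alter which contrast was powered.

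**The case against.** The best defence is that the abstract is only a condensed sentence and the body is clear enough on the contrast. Design, Outcome measures, and Sample size and statistics all compare randomised arms, and no section plans an uncontrolled before-after test as the primary analysis. That stands: the uncontrolled reading comes from the abstract alone. Tables 1 and 2 are also not in the text available here, and Table 2 summarises the outcome measures, so a unit may be given there. This limits what can be said about the missing unit. It does not reconcile the abstract with the body, settle whether single-QI changes or the sum score is the main outcome, or make baseline adjustment anything but optional.

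A reader might go further and infer that the abstract's outcome uses prescriptions as its denominator, so that an intervention which discourages prescribing would shrink the denominator and hide part of its own benefit. The document does not support that. The abstract names no denominator. The sample-size section counts inappropriate prescription per 100 patients. Several QIs concern drug combinations or three or more concurrent psychotropics, which describe a patient's regimen rather than a single prescription. No per-prescription analysis is planned. Any such distortion would also depend on how total prescribing moved, for which there is no figure, and it would reverse if prescribing rose.

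**Conclusion.** The main outcome is stated inconsistently and should be fixed in one form. The contradiction in contrast is in the current text and needs no assumption. The 80% power with 74 groups applies to hits per 100 patients compared between arms at follow-up, and to no other version in the document.

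The size of the discrepancy between a change from baseline and the powered contrast depends on control-arm drift: none if controls stay at 25, and 2.5 hits per 100 (8 against 5.5) under an assumed 10% fall. The protocol gives no drift figure, but it does raise the possibility.

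This is a defect of definition and pre-specification. It does not show that the planned analysis is biased, because the analysis described in the body is a randomised comparison.

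**What to change.** Use one statement of the main outcome in the abstract, Outcome measures, and Sample size and statistics: QI hits summed over the indicators in the sum score, per 100 patients aged 70 or over, in the 12-month follow-up window, compared between randomised arms at the level of the peer group.

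Make the group's baseline rate a pre-specified covariate in that comparison, used whether or not imbalance is seen, in place of optional covariance analysis. Report individual QIs and within-arm changes from baseline as secondary. Confirm that the pilot figure of 25 hits was counted over the same set of indicators as the sum score.

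The cost is edits to three sections and one firm analysis commitment. Baseline and follow-up data are already planned for both arms, so nothing new is collected. The 74 groups carry over as calculated, in so far as hits are treated as a proportion, and the covariate can be expected to improve precision.

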**Discussion:**

Improvement of prescription patterns in medical practice is a challenging task. Evidence suggests that a thorough evaluation of diagnostic indications for drug treatment in the elderly and/or a reduction of potentially inappropriate drugs may impose significant clinical benefits. Our hypothesis is that an educational intervention program will be effective in improving prescribing patterns for elderly patients in GP settings.

## Background

Although appropriate use of drugs may indeed be of vital importance to elderly patients, drugs represent a double-edged sword due to their potential adverse effects. Age-related changes in drug metabolism and sensitivity put frail elderly patients at particular risk for adverse drug events (ADEs) [1,2]. The Word Health Organization (WHO) defines an ADE as a detrimental response to medication that is undesired and unintended, excluding therapeutic failure, poisoning, and intentional overdose [3]. In the elderly, between 10 and 20% of all hospital admissions are drug-related [4-8] and also associated with a higher mortality than other reasons for hospitalization [4]. In a comprehensive study from a large internal medical department in Norway, more than one out of six deaths were judged to be caused by the drug treatment used rather than the underlying illness [9]. According to the WHO, rational use of drugs implicates "each patient receiving medication appropriate for his/her clinical needs, in doses meeting the related requirements, for an adequate period of time and at the lowest cost to them and to community" [10].

Inappropriate us of drugs commonly occur in the elderly and may imply impaired quality of life and drug related morbidity and morbidity [4,11-15]. Problems related to GPs' lack of updated medication lists for their patients [16], the common practice of prescribing for patients without seeing them [17,18], inadequate communication between physicians and community nurses regarding treatment for shared care patients [16], and patients' noncompliance, as well as physicians' lacking ability to understand, detect, and improve compliance, also increase the risk of medical errors and ADEs [19].

In the Norwegian general practice *Møre & Romsdal Prescription study*, Straand and Rokstad [15] considered 13.5% of 16774 prescriptions for elderly patients to be inappropriate. Corresponding figures have been reported by Stuck et al. [20], who found that 14% of 414 patients older than 75 years used at least one inappropriate drug. Willcox et al. [17] found that potentially inappropriate drugs were prescribed for 23.5% of 6 171 patients 65 years and older. However, the different studies apply different criteria for inappropriateness. Based on Beers criteria [20], Aparasu and Mort [21] reviewed eight studies on prescription patterns in elderly, and found that the rate of inappropriate drug use varied from 14% in community-dwelling elderly to 40.3% in nursing home residents.

Prescribing indicators for general practice have been used for more than two decades [22]. Previous research has highlighted the importance of a critical approach to prescribing practice [23,24], the defining and assessment of the appropriateness of prescribing [25,26], the exploration of variations in prescribing across general practices [27], and the physicians' adherence to various standards [28]. However, few validated quality indicators exist for prescribing in general practice [29], and published standards tend to be consensus-based rather than evidence-based.

Quality indicators (QIs) are explicitly defined and measurable items which may serve as building blocks in the assessment of care [30]. As statements about structure, process, or outcomes they may be used to generate criteria and standards to measure specific aspects of clinical practice [31]. Indicators differ from guidelines, review criteria, and standards and may be regarded as a kind of rules of the thumb. Primary care rarely meets absolute standards [32], and the development of indicators must be realistic and set according to context and patient circumstances [33]. Indicators can measure the frequency with which an event occurs, such as prescriptions of a particular drug. However, indicators do not provide definite answers, they rather *indicate *potential problems. Quality measures are now increasingly being developed for primary care quality assessments and research [30]. This development has probably been encouraged by the increased access to large health care databases, made up by automated electronic records of e.g. filled prescriptions, professional services, and hospitalizations [34]. Linking prescription databases with various electronic patient record (EPR) systems comprising detailed information of patients' symptoms, findings and diagnoses enables a "reality-based" pharmaco-epidemiologic research, which may be useful for highlighting areas in need of quality improvements.

The identification of suboptimal practice is, however, only the first step for quality improvements. Several educational strategies have been used to improve doctors' clinical practice, but substantial effects are only rarely reported [35,36]. Rokstad et al. [37] performed a controlled educational intervention towards GPs aimed at improving their prescriptions for acute cystitis and insomnia. The intervention included mailed prescription feedback along with printed therapeutic recommendations, and resulted in statistical significant (although clinically moderate) improvements in prescription patterns in the intervention group (GPs in one district), compared to the control group (GPs in another district) [37]. Davies et al. [38] reviewed 777 continuous medical education (CME) studies and found evidence that educational intervention consisting of passive dissemination of clinical practice guidelines had little or no effect on practice. This corresponds with later reports by Oxman et al. [36] and Freemantle et al. [39]. More active strategies, like educational outreach visits [40,41] and multifaceted interventions [35], are more effective, but require more resources [35]. In an extensive review, Jamtvedt et al. [41] concluded that audit and feedback may be effective in improving professional medical practice, although the effects are generally moderate, and that absolute effects of audit and feedback are more likely to be larger when baseline adherence to recommended practice is low.

Underlying reasons for deviations between clinical practice and clinical guidelines vary from one problem to another and from one physician to another [42]. Therefore, it is recommended to address potential barriers to change when tailoring an intervention targeting change in medical performance. Because non-equivalent comparison groups may distort the results of evaluations, cluster-randomized trials (in which healthcare professionals or groups of professionals, rather than patients are randomized) are more likely to provide valid results than other research designs, such as controlled before-after or time-series studies [43].

We have developed an intervention aimed at improving GPs' prescribing practice for elderly (≥ 70 years) out-patients, and planned a cluster randomized controlled trial to assess the effectiveness of this intervention.

## Methods

### Design

Our hypothesis is that an educational intervention program carried out during a 6-month period will be effective in improving prescribing patterns by reducing the occurrence of potentially targeted harmful drugs and drug-drug interactions in elderly patients.

Our main hypothesis will be tested using a cluster-randomized controlled trial comparing outcomes between the intervention and control groups at follow-up. Peer continuing medial education (CME) groups of GPs will be randomized to receive a tailored intervention to support a safer prescription practice for the elderly or to a control group. The control group will be assigned to another trial, namely an educational intervention for better prescription of antibiotics for respiratory tract infections [44]. As such, the control group may also be susceptible to changes in their general prescription patterns, i.e. a possible Hawthorne effect. To control for this, we will be able to analyze prescription patterns for *all *Norwegian GPs not included in the current trial, using data from the Norwegian Prescription Database (NorPD), a national registry including data for all prescription drugs issued at Norwegian pharmacies, established in 2004 [45].

Prescription data will be collected for all eligible patients from intervention- and control group GPs at baseline and one year after the initiation of the trial. Changes in prescribing patterns will be tracked by a set of explicit recommendations (quality indicators) developed by the authors (Table 1), which will be used to analyze changes in baseline and post-intervention prescribing patterns. Degree of improvements will be measured by recording prescriptions of the particular drugs and the concurrent use of listed drug combinations that the GPs have been recommended to avoid.

